| Sponsor                            | University College London (previously MRC)                                                                                                                                                                                                                                                                                                                                                                                                                                                                                                                                                                                                                                                                                                                                                                                                                                                                                                                                                                                                                                                                                   |
| Legal Representative in Europe     | UCL Research Limited, Dublin, Ireland                                                                                                                                                                                                                                                                                                                                                                                                                                                                                                                                                                                                                                                                                                                                                                                                                                                                                                                                                                                                                                                                                        |
| Interventions to be Compared       | There are two interventions, radiotherapy and hormone therapy. See Figures 1, 2 and 3 .                                                                                                                                                                                                                                                                                                                                                                                                                                                                                                                                                                                                                                                                                                                                                                                                                                                                                                                                                                                                                      |
| Study Hypothesis                   | 
RADICALS-RT: That the use of early post-operative radiotherapy would improve long-term clinical outcomes after radical prostatectomy
 
RADICALS-HD: That the use of hormone therapy would improve long-term clinical outcomes in men receiving post-operative radiotherapy after radical prostatectomy, and that long-term hormone therapy would be more effective than short-term hormone therapy
                                                                                                                                                                                                                                                                                                                                                                                                                                                                                                                                                                                                                                                                                                               |
| Primary Outcome Measure(s)         | 
RADICALS-RT:
Freedom-from-distant-metastasis (FFDM)
 
RADICALS-HD:
Metastasis-free-survival (MFS)
                                                                                                                                                                                                                                                                                                                                                                                                                                                                                                                                                                                                                                                                                                                                                                                                                                                                                                                                                                                                        |
| Secondary Outcome Measure(s)       | 
 
• Disease-specific survival (DSS) (RADICALS-RT only)
 
• Freedom from treatment failure: PSA progression when on androgen deprivation
 
• Freedom from distant metastasis (FFDM) (HD only)
 
• Clinical progression-free survival (PFS): Clinical progression of prostate cancer or initiation of non-protocol hormone therapy or death from prostate cancer.
 
• Overall survival (OS): Death from any cause
 
• Non-protocol hormone therapy: Initiation of hormone therapy other than that randomised
 
• Treatment toxicity: Incidence of severe toxicity or serious adverse events. Radiotherapy treatment planning data is required to understand the cause of treatment toxicity.
 
• Patient reported outcomes: See Section 13.1 for details
 
• Freedom from biochemical progression: Where a biochemical progression event is defined as a PSA level of <math>\geq 0.4</math>ng/ml following radiotherapy or a PSA level of <math>> 2.0</math>ng/ml regardless of prior radiotherapy.
 
 |
| Randomisation                      | 1:1 (RT) +/- 1:1:1 (HD)                                                                                                                                                                                                                                                                                                                                                                                                                                                                                                                                                                                                                                                                                                                                                                                                                                                                                                                                                                                                                                                                                                      |

| SUMMARY INFORMATION TYPE                    | SUMMARY DETAILS                                                                                                                                                                                                                                                                                                                                        |
|---------------------------------------------|--------------------------------------------------------------------------------------------------------------------------------------------------------------------------------------------------------------------------------------------------------------------------------------------------------------------------------------------------------|
| Number of Participants to be Studied | A total of 1396 patients were recruited into RADICALS-RT and 2840 patients into the RADICALS-HD. Many patients contributed to both randomisations. Patients were permitted to be randomised between two of the three arms in RADICALS-HD. For more details refer to Section 9 . The trial completed recruitment on 30th December 2016. |
| Duration                             | Trial outcomes for RADICALS-RT and HD are planned to be assessed in 2022.                                                                                                                                                                                                                                                                              |
| Funder                               | CRUK and MRC (UK)
CCTG (Canada)                                                                                                                                                                                                                                                                                                                     |
| Chief Investigator                   | [name]                                                                                                                                                                                                                                                                                                                                 |

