## TRIAL DURATION

The trial was originally planned to address these questions over 12-13 years with 5½ to 6½ years of accrual and around 7 years of further Follow-up. The IDMC has advised that overall event rates have been much lower than anticipated. This prompted a change of primary outcome in the RADICALS-RT comparison (changed in protocol V4.0 from disease-specific survival to freedom from distant metastasis). The IDMC subsequently advised that event rates are lower still (without reference to comparative data by arm).

Following updated projections in 2019, the IDMC and TSC also supported the proposal for the change in primary outcome for RADICALS-HD from disease-specific survival to metastasis free survival, based on the findings from the IcECaP study. This proposal was also approved by the trial funder.

The patient group is men with non-metastatic adenocarcinoma of the prostate who have had a radical prostatectomy. Treatment duration within the trial will range from zero months (i.e. a proportion of patients, maybe 60%, allocated to deferred radiotherapy will never need it) to 24 months (for patients allocated long-term hormone therapy). Follow-up is required every 4 months for 2 years, every 6 months from 2 to 5 years and then annually. This broad patient group has a good long-term prognosis and full, long-term Follow-up data are essential to understand the impact of these treatments. For more details refer to [Section 7.1](#).

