#### 6.2.1 PRIMARY OUTCOME MEASURE - RADICALS-RT

RADICALS-RT was originally designed to detect an absolute improvement of 5% in disease-specific survival at 10-years from 90% to 95% with 80% power. Since the trial was designed in 2006, further information on disease-specific survival in similar patient cohorts has become available from prospective RCTs, including EORTC 22911 (8) and SWOG 8794 (10). These provide useful estimates as they are both clinical trials and recruited partly during the PSA era; such information was not previously available. The results of these trials show that death from causes other than prostate cancer is a major competing risk, with around only one in four deaths being attributed to prostate cancer and a 10-year disease-specific-survival (DSS) of around 94%; this patient cohort is performing much better than had been anticipated originally. With further treatments (e.g. docetaxel) being available and standard of care at the time of relapse and the development of castrate-refractory disease, the time from the development of distant metastasis until death from prostate cancer has lengthened. An absolute improvement of 5% is not a reasonable assumption if these estimates hold true.

However, the role of adjuvant RT remains controversial and a clinical trial is required to resolve this issue. RADICALS-RT will do this. Therefore, focus has turned towards distant metastases, which is an earlier but clinically important and objective outcome measure. The primary outcome measure for RADICALS-RT is now **freedom-from-distant-metastasis**.

Disease-specific survival, therefore, becomes an important secondary outcome measure. At the main analysis of distant metastases, the trial would expect around 41 deaths from prostate cancer and would have 59% power to detect a halving of the risk of prostate cancer death from 6% at 10-years to 3%, ie DSS improves from 94% to 97%. With further follow-up, RADICALS-RT could attain 80% power for DSS after additional 6 years of follow-up (total duration of the trial would be 18.5 years). However, the question of DSS would be addressed sooner through combined analysis with two parallel trials: RAVES and GETUG-17 (see [Section 9.6](#)).

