### 6.2.4 EARLY REPORTING OF BIOCHEMICAL OUTCOMES

In early 2018, based on the number of primary outcome events in the control arm of the RADICALS-RT comparison, the target number of events was not forecast to occur until 2025. This is several years later than originally expected due to the low event rate. Two other randomised controlled trials (RCTs), RAVES and GETUG 17, also address the question of deferred RT and are planning to report in 2018/2019. The ARTISTIC project is a pre-planned individual patient data meta-analysis, combining RAVES, GETUG-17 and RADICALS-RT. The RADICALS TMG therefore agreed, in February 2018, to publish the Freedom from biochemical progression results of RADICAL-RT to coincide with the other two trials, and enable a timely meta-analysis.

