### 6.3.2 RADICALS-RT SAMPLE SIZE

In the patients suitable for this randomisation, the control arm is assumed to be deferred radiotherapy i.e. radiotherapy at PSA relapse.

When the trial was originally designed, there was uncertainty about the likely event rate but it was anticipated that a modest absolute effect in the order of 5% would be required to convince clinicians to adopt adjuvant radiotherapy for all patients. The original sample size calculations anticipated that around 2,600 patients would need to be recruited over 5½ years and followed-up for a further 7 years in order to obtain 80% power to detect an improvement from 70% to 75% or 90% power to detect an improvement from 80% to 85%.

From SWOG 8794 and EORTC 22911, the proportion of patients free of distant metastases at 10 years is estimated to be 90%. We would look to test whether adjuvant RT can improve this to 95% (hazard ratio 0.487), which is seen as the minimum clinically significant improvement required to routinely introduce adjuvant RT to this patient population; this mirrors the size effect observed in SWOG 8794. This is tested using the superiority design. With 80% power, a two-sided 5% significance level, accrual lasting 5½ years (reaching peak accrual rates after 3 years) and a further 7 years of follow-up, we would need to recruit 1,063 patients in order to observe 66 distant metastases events. This sample size assumes that 30% of patients are lost to follow-up and around 30 patients per month randomised from 30 months onward. Therefore, the target sample size will be reduced from 2,600 to around 1,063 patients. This assumes that 30% of patients are lost to follow-up between 5 and 10 years.

If the peak accrual is lower, at around 25 patients per month, accrual would be extended by 1 year, to around 6½ years and around 1,160 patients would be randomised; this should address the question with the same power and in the same overall timescale.

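### RADICALS-RT outcomes are to be assessed in 2022, yet the only stated forecast puts the target primary events in 2025; if it still holds, the stated 80% power does not apply in 2022

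*Combined protocol and SAP*

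**What the plan says.** Section 6.2.1 names the endpoint: "The primary outcome measure for RADICALS-RT is now freedom-from-distant-metastasis". Section 6.3.2 sets the design. It starts from "With 80% power, a two-sided 5% significance level" and takes a 10-year rate free of distant metastasis that rises from 90% to 95% (HR 0.487). It concludes that "we would need to recruit 1,063 patients in order to observe 66 distant metastases events". The accrual and follow-up assumed there are 5½ years plus 7 years. In fact 1396 men were recruited (Trial Summary) and randomisation closed in June 2015 (section 3.2).

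Two dates are given for what follows:

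- Trial Summary, Duration: "Trial outcomes for RADICALS-RT and HD are planned to be assessed in 2022".
- Section 6.2.4, on the position in early 2018 as projected from control-arm primary events: "the target number of events was not forecast to occur until 2025".

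The Trial Duration section adds that "The IDMC subsequently advised that event rates are lower still". It also mentions projections updated in 2019, but only as the reason for changing the RADICALS-HD primary outcome. Sections 6.3.3.A and 6.3.3.B give updated power for the two HD comparisons at the numbers actually recruited. Section 6.3.2 has no such update for RT.

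**The concern.** The 80% power in section 6.3.2 belongs to 66 events. If those events arrive only in 2025, an FFDM analysis in 2022 is done on fewer, and its power at HR 0.487 is below 80%. The protocol does not say whether the RT primary analysis waits for the events or goes ahead by date.

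Two things are at stake. First, a non-significant result from an early analysis would be read against a power that the analysis did not have. Second, in an open-label trial the timing of the primary analysis should be fixed by a written rule and not left open.

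A related point concerns the target itself. A later forecast means a lower event rate than the 90% control figure implies, so the same HR represents a smaller absolute gain than the 5 points in section 6.3.2.

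**Working it through.** **Step 1. Reproduce the plan's target.** HR = ln(0.95)/ln(0.90) = 0.487. With Freedman's formula, D = [(1.960 + 0.842)(1 + HR)/(1 − HR)]² = [2.802 × 1.487/0.513]² ≈ 66. The 66 events reproduce. Schoenfeld's formula gives 61, so Freedman's is the one that matches. It also matches section 6.2.1: for 41 prostate cancer deaths and survival rising from 94% to 97%, HR = ln(0.97)/ln(0.94) = 0.492 and power = 58.7%, against a stated 59%.

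**Step 2. Project events in 2022.** The protocol gives no RT event count, so this step rests on assumptions.

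- From the protocol: 1396 men, 1:1 allocation, accrual ending mid-2015 and peaking after 3 years, HR 0.487.
- Assumed: accrual starting around late 2007 (mid-2007 to early 2008 was tried); losses of none, 30% by 10 years, or 30% between years 5 and 10; target events reached at the start, middle or end of 2025; analysis at the start, middle or end of 2022.
- Also assumed: the target in section 6.2.4 is the 66 of section 6.3.2, which section 6.2.4 does not repeat.

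The hazard was scaled to give 66 events in 2025, and events were then counted in 2022:

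- Constant hazard: roughly 48 to 58 events. The least favourable corner gives 47.
- Rising hazard (Weibull shape 1.3 to 1.6): about 40 to 55 events. The least favourable corner gives 38.

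**Step 3. Power and detectable HR.** Power = Φ(√D × (1 − HR)/(1 + HR) − 1.96), where (1 − 0.487)/(1 + 0.487) = 0.345. The HR detectable with 80% power is (1 − k)/(1 + k), where k = 2.802/√D.

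| Events | Power at HR 0.487 | HR detectable with 80% power |
|---|---|---|
| 40 | 58.8% | 0.386 |
| 48 | 66.7% | 0.424 |
| 55 | 72.5% | 0.452 |
| 58 | 74.8% | 0.462 |
| 66 | 80.0% | 0.487 |

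With 47 events power is 65.7%. Hence about 66% to 75% under a constant hazard and about 59% to 73% under a rising one.

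**Step 4. Absolute effect.** With a 90% control rate and HR 0.487, the same model has 1396 men passing 66 events between about 2018 and 2020. A 2025 forecast therefore implies a lower event rate. Under a constant hazard it implies a 10-year control rate of roughly 94% to 95%. The gain is S^0.487 − S:

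- S = 0.900: 0.950 − 0.900 = 5.0 points
- S = 0.937: 0.969 − 0.937 = 3.2 points
- S = 0.952: 0.976 − 0.952 = 2.4 points

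**The case against.** Four points can be made on the other side.

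*The forecast may be out of date.* It was made in early 2018 and is cited to explain early biochemical reporting. The amendment log (section 14.1.8) shows that the duration row was added in version 7.0, dated February 2020, after projections had been updated in 2019. This stands as a caution: the 2025 date may have been replaced. But version 7.0 still carries it, gives no new RT date, and ties the 2019 projections only to HD.

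*The 2022 row may not mean the primary analysis.* A reader might infer that the trial has dropped its event target for a calendar-driven primary analysis. The documents do not support that. The row speaks of trial outcomes and names no endpoint, sections 6.2.4 and 6.3.2 are framed by events, and section 6.5 leaves analysis detail to a separate plan in which a trigger could sit. What remains is that the row names RT alongside HD without excluding FFDM.

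*The event count is conditional.* The forecast rested on control-arm events. At HR 0.487, 66 events contain about 66/1.487 = 44 control events. If the forecast is matched to 44 control events and the true HR is nearer 1, total events in 2022 under a constant hazard would be about 57 to 71 at HR 0.8 and 63 to 78 at HR 1. So a null result in 2022 could contain 66 or more events. This stands, and it rules out saying flatly that the analysis will have some 50-odd events. It does not restore the stated power, because power at HR 0.487 must be computed at the events expected when that HR is true.

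*The 5-point target.* A reader might infer that the protocol has already called a 5-point gain unreasonable. Section 6.2.1 says so only of disease-specific survival, and only on condition that the external estimates hold. Section 6.3.2 still presents 90% to 95% as the smallest gain that would change practice.

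**Conclusion.** The two dates stand unreconciled in the current text, and on the protocol's only stated RT forecast the 80% power does not carry over to an FFDM analysis in 2022. The direction is certain if the 2025 forecast holds and HR 0.487 is true; the size is not. Power is roughly 66% to 75% under a constant hazard, a loss of about 5 to 14 points, and about 59% to 73% if the hazard rises. These ranges depend on the assumed accrual start, loss pattern, hazard shape and point within each year. The implied gain of 2.4 to 3.2 points rests on the same assumptions with a constant hazard.

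The documents do not settle whether the 2025 forecast is still current, whether 2022 was meant for FFDM, or whether 2022 was meant for HD alone. This is an inconsistency that should be fixed, held with medium confidence. It is not evidence that an underpowered primary analysis has been chosen.

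**What to change.** Reconcile the Duration row, section 6.2.4 and section 6.3.2 in one of two ways:

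- State that the RADICALS-RT FFDM primary analysis is triggered by 66 events, and give the sponsor's current forecast date.
- If the 2022 date stands for RT, restate power at HR 0.487 and the HR detectable with 80% power, at the number of events the sponsor now projects for 2022.

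The sponsor holds the event counts, so its own projection should be used and not the ranges above. In section 6.3.2, also give the absolute difference that HR 0.487 represents at the currently projected control rate, next to the 90% to 95% statement.

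The cost is a few sentences in three places. The downside is either a later RT result or a less favourable stated power.
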